### Sample size considerations

For the primary endpoint, we expect an overall composite complication rate (OCCR) of about 25% at 90 days after surgery. This guestimate is based on a subgroup of elderly patients included in a large observational study in the field of Patient Blood Management [29], which reported most of the endpoint components, and is also based on the assumption that about 25–40% of registered patients will be randomised.

The effect size to be detected is set to an odds ratio of OR = 0.765. The available evidence on treatment differences from randomised trials concerning the old age group is sparse and inconsistent. Therefore, we choose an effect size, which is relevant from a clinical perspective. Assuming an OCCR of 25%, an odds ratio of OR = 0.765, corresponding to a 5% reduction in OCCR from 27.5% to 22.5% or risk reduction of 18%, would justify switching to the liberal transfusion strategy.

The target sample size is *N* = 2470 randomised patients. Randomisation of 2 × 1176 = 2352 patients is required using a two-sided significance level of 5% and requiring power of 80% for a test of the null-hypothesis OR = 1 versus OR = 0.765 based on the normal approximation to log (OR). We allow for a dropout rate of up to 5%.

### Statistical analysis

The full analysis set for the primary efficacy analysis will be as close as possible to the ideal implied by the intention-to-treat principle and includes all randomised subjects. A secondary per-protocol analysis of the primary outcome will be performed in all patients without major protocol violations.

Most endpoints will be analysed with scale-appropriate generalised linear mixed models adjusting for age, cancer surgery (y/n), type of surgery (intermediate- or high-risk), and incorporating centres as random effect. Further baseline clinical variables may be entered in secondary analyses.

For the primary endpoint, logistic regression will be used to estimate the treatment effect on the odds ratio scale with two-sided 95% confidence intervals provided. Secondarily, also point estimates and confidence intervals for the rate difference and the relative risk will be provided. The test of the null hypothesis that the odds ratio concerning the composite endpoint is equal to one will be tested using the Wald statistic for the coefficient of the treatment effect in the logistic regression.

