### Secondary endpoints

**Secondary outcome** measures are the following:The occurrence of any individual component of the composite at hospital discharge, at 90 days, and 1 year after surgery.Proportion of patients receiving RBC transfusion and the number of units transfused.Total length of stay in the intensive care unit and in hospital from randomisation to discharge (for strategy comparison); in addition, total length of stay in the intensive care unit and in hospital from admission to discharge will be used for descriptive purposes.The occurrence of acute kidney injury (stage I or II) defined according to the Kidney Disease Improving Global Outcomes criteria [21] (stage I: increase of plasma creatinine level ≥ 1.5–1.9 times baseline or ≥ 0.3 mg/dl within 48 h; stage II: increase of plasma creatinine level ≥ 2–2.9 times baseline within a time window of 7 days) during the initial hospital stay.Time to (first) infection (infection requiring therapeutic intravenous antibiotic treatment (pneumonia, wound infection, sepsis, central line associated blood stream infection [21–23])) during the initial hospital stay or leading to hospital re-admission within 90 days after surgery.Time to (first) re-hospitalisation within 90 days.Functional status (assessed by Barthel Index [24, 25] by telephone questionnaire).Health-related quality of life (assessed by EuroQoL EQ-5D [26, 27] and 12-item World Health Organisation Disability Assessment Schedule WHODAS 2.0 [28] by telephone questionnaire).

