### Analysis in the larger set of all registered patients

We collect course of Hb levels during surgery (= day 0) or day 1, 2, 3 after surgery and the vital status at day 90 (all-cause mortality) for all registered patients.

The prognostic value of delta Hb (difference pre-op Hb and Hb on day three) and Barthel index on short term mortality will be analysed adding these factors to the generalised linear mixed model specified above.

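### The covariate set stated for most endpoints has no baseline value of the outcome; if it is applied to the Barthel Index, the functional comparison loses precision, though it is not biased

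*Protocol article*

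**What the plan says.** Three places in the protocol article bear on this.

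- **Statistical analysis** gives one general model: "Most endpoints will be analysed with scale-appropriate generalised linear mixed models adjusting for age, cancer surgery (y/n), type of surgery (intermediate- or high-risk"), with centre as a random effect. The sentence that follows is permissive and names no variable: "Further baseline clinical variables may be entered in secondary analyses".
- **Secondary endpoints** lists among the outcomes "Functional status (assessed by Barthel Index [24, 25] by telephone questionnaire"). EQ-5D and WHODAS 2.0, also by telephone, come next in the list.
- **Analysis in the larger set of all registered patients** plans to study "The prognostic value of delta Hb (difference pre-op Hb and Hb on day three) and Barthel index on short term mortality", and does so by adding these factors to the mixed model given earlier.

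No section gives the Barthel outcome a model of its own.

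**The concern.** For a score measured before and after treatment, the patient's own earlier value is usually the strongest single predictor of the later one. In patients aged 70 or over, prior function is likely to explain a good part of later function. The general covariate set leaves it out, while the analysis of all registered patients treats the Barthel score as prognostic and as an addition to that same model. The score therefore appears to be available, and it is not already in the model.

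At stake is the width of the confidence interval for the effect of strategy on functional status. A chance difference between the arms in baseline function would also go unadjusted, but that is the same loss of precision seen from another side and not a second harm. If baseline function is added only later, as an optional variable, the choice is open to the criticism that it was made with the data in view.

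**Working it through.** **Inputs from the article**

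- Covariates: age, cancer surgery, surgery risk, and centre as a random effect (Statistical analysis).
- Two-sided 5% level, 80% power, 2 × 1176 = 2352 patients before the dropout allowance (Sample size considerations).
- Standard deviation, target difference, power and baseline correlation for the Barthel Index: none stated.

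**The plan's own figure.** The only sample size is for the primary endpoint. With rates of 27.5% and 22.5% and OR = 0.765:

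n per arm = (1.960 + 0.842)² × [1/(0.275 × 0.725) + 1/(0.225 × 0.775)] / (ln 0.765)² = 7.849 × 10.750 / 0.07176 ≈ 1175.9, so 1176.

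This agrees with the article. It shows that 2352 is the evaluable number to use below; the present point does not alter it.

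**Is a baseline score available?** A prognostic factor for death has to be measured before death. According to the Study population section, patients whose Hb stays above 9 g/dl do not enter the main study and have vital status determined at 90 days. A Barthel score used as a predictor across all registered patients is therefore most plausibly taken at registration. This is an inference: the section names no time point, and the schedule in Fig. 1 is not shown.

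**Precision.** Let r be the partial correlation between baseline and follow-up Barthel score, given the covariates already in the model. The article gives no value, so r is assumed. In a linear model, adding the baseline score multiplies the variance of the treatment estimate by 1 − r² and the interval width by √(1 − r²). This ratio does not depend on the number of patients.

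| Assumed r | 1 − r² | √(1 − r²) | Interval narrower by |
|---|---|---|---|
| 0.3 | 0.91 | 0.954 | 4.6% |
| 0.5 | 0.75 | 0.866 | 13.4% |
| 0.7 | 0.51 | 0.714 | 28.6% |

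**Absolute scale.** With 1176 per arm and complete Barthel data, the difference detectable at 80% power without the baseline score is 2.802 × √(2/1176) = 0.116 residual SD. With the score it is that figure times √(1 − r²): 0.110, 0.100 and 0.082 at r = 0.3, 0.5 and 0.7. At a true difference of 0.1 residual SD, chosen only for illustration, power is 68% without the score and 72%, 80% and 92% with it.

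Deaths and missed telephone contacts will leave fewer than 2352 scores, so the absolute figures are optimistic. The percentages in the table do not change with the number of patients.

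**The case against.** The strongest objection is that this is a condensed article. Covariates for individual secondary endpoints are commonly settled in the full protocol or the SAP, neither of which is shown. The general sentence covers most endpoints, not all, and does not name the Barthel Index. The sentence on further baseline variables leaves room for more terms. A reader might infer that the plan has fixed a Barthel model without baseline function; the text does not say so.

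Much of this stands, and it is why the point is conditional. It does not remove the point. The article is not silent: it states a covariate set meant to reach outcomes on different scales, and a score such as the Barthel Index is an evident candidate. Further variables are only permitted, none is named, and they are placed in secondary analyses. An SAP with the baseline score in the main Barthel model would go beyond what is written here.

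Two further objections are fair. First, the practical loss may be modest: about 0.116 residual SD is detectable even without the baseline score. Second, the Barthel Index is a bounded score. If a non-linear model is chosen, the factor 1 − r² is only a rough guide.

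**Conclusion.** The point holds in conditional form and is minor. If the stated covariate set is applied to the Barthel outcome, the comparison gives up precision that one extra covariate would recover: about 5%, 13% or 29% of the interval width at r = 0.3, 0.5 or 0.7. This rests on three assumptions: that the general set is meant for the Barthel outcome, that a pre-operative score is collected, and that r lies in this range with a roughly linear model.

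Three stronger readings are tempting and are not supported:

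- **That the comparison is biased.** Allocation is randomised, so leaving out a baseline covariate costs precision only. With 1176 per arm, the standard error of a baseline mean difference is √(2/1176) ≈ 0.04 SD, so large chance imbalance is unlikely.
- **That EQ-5D and WHODAS 2.0 have the same defect.** Nothing in the text shows a pre-operative value for either.
- **That a specific amount of power is lost.** The article states no power for the Barthel Index; any such figure depends on an assumed effect and an assumed r.

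The primary analysis, significance level and sample size are untouched.

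**What to change.** State, in the full protocol or the SAP, that the main model for the Barthel outcome includes the pre-operative Barthel score as a covariate, with all other terms unchanged. Add a simple rule for missing baseline scores, for example imputing the overall baseline mean without regard to arm, so that no randomised patient is dropped for this reason. Confirm against the assessment schedule that the score is taken before surgery. Apply the same wording to EQ-5D and WHODAS 2.0 only if a pre-operative value is in fact collected.

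The cost is a line or two of wording and one degree of freedom. If the pre-operative score is collected as the text implies, no new data, visits or patients are needed; if it is not, the change to the model does not apply.

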**Methods:**

The LIBERAL Trial is a prospective, randomized, multicentre, controlled clinical phase IV trial randomising 2470 elderly (≥ 70 years) patients undergoing intermediate- or high-risk non-cardiac surgery. Registered patients will be randomised only if Haemoglobin (Hb) reaches ≤9 g/dl during surgery or within 3 days after surgery either to the LIBERAL group (transfusion of a single RBC unit when Hb ≤ 9 g/dl with a target range for the post-transfusion Hb level of 9–10.5 g/dl) or the RESTRICTIVE group (transfusion of a single RBC unit when Hb ≤ 7.5 g/dl with a target range for the post-transfusion Hb level of 7.5–9 g/dl). The intervention per patient will be followed until hospital discharge or up to 30 days after surgery, whichever occurs first. The primary efficacy outcome is defined as a composite of all-cause mortality, acute myocardial infarction, acute ischaemic stroke, acute kidney injury (stage III), acute mesenteric ischaemia and acute peripheral vascular ischaemia within 90 days after surgery. Infections requiring iv antibiotics with re-hospitalisation are assessed as important secondary endpoint. The primary endpoint will be analysed by logistic regression adjusting for age, cancer surgery (y/n), type of surgery (intermediate- or high-risk), and incorporating centres as random effect.

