### Planned exploratory sub-group analyses

We hypothesise that the benefit from a liberal transfusion strategy increases with declining anaemia compensatory capacity.

We will therefore perform exploratory subgroup analyses byAge (< 80 versus ≥80 years),Gender (male/female),American Society of Anaesthesiology Physical Status classification [30],presence of cancer (y/n),ischaemic heart disease (y/n),heart failure (y/n),peripheral vascular disease (y/n),previous stroke (y/n),

Any resulting hypothesis requires confirmation in independent data.

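### The primary model leaves out ASA class, cardiovascular comorbidities and pre-operative Hb, which the trial records anyway, and so forgoes a modest and uncertain gain in power

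*Protocol article*

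**What the plan says.** The Abstract (Methods) fixes the model for the primary endpoint as logistic regression "adjusting for age, cancer surgery (y/n), type of surgery (intermediate- or high-risk), and incorporating centres as random effect". The Statistical analysis section repeats this set, tests the treatment coefficient with a Wald statistic, and adds: "Further baseline clinical variables may be entered in secondary analyses". The rate difference and the relative risk are to be reported as well.

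Other baseline variables are needed elsewhere in the plan:

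- Planned exploratory sub-group analyses lists "American Society of Anaesthesiology Physical Status classification" together with ischaemic heart disease, heart failure, peripheral vascular disease and previous stroke.
- Pre-operative Hb decides eligibility at registration (Study population). It is also one half of the delta Hb variable in the section on all registered patients.

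On size, Sample size considerations states: "The effect size to be detected is set to an odds ratio of OR = 0.765". It describes this as "corresponding to a 5% reduction in OCCR from 27.5% to 22.5% or risk reduction of 18" per cent. It then says "Randomisation of 2 × 1176 = 2352 patients is required", "using a two-sided significance level of 5% and requiring power of 80" per cent. The calculation contains no covariate term.

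**The concern.** The Background and Discussion argue that cardiovascular comorbidity and reduced functional reserve leave elderly patients more vulnerable to ischaemic events and perioperative complications. On that reasoning the comorbidity variables should carry information about a composite of death and ischaemic events, but none of them is in the primary model. Randomisation is stratified by centre only, so the design does not balance them either.

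In a logistic model, omitting a prognostic covariate pulls the treatment odds ratio towards 1 and lowers the power of the Wald test, even under perfect randomisation. The trial is sized at 80% with no reserve, on an event rate that the protocol itself presents as a rough guess. A few points of power from data already in hand would be worth having. At stake is that increment, not the validity of the analysis.

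**Working it through.** **1. The plan's own figure.** Inputs from Sample size considerations: two-sided 5%, power 80%, rates 27.5% and 22.5%, OR 0.765.

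n per arm = (z₀.₉₇₅ + z₀.₈₀)² × [1/(p₁(1−p₁)) + 1/(p₂(1−p₂))] / (ln OR)²

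= 7.849 × (5.016 + 5.735) / 0.07176 = 1175.9, so 1176 per arm and 2352 in total. Power at 1176 per arm is 80.0%. The figure reproduces exactly, without any covariate.

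**2. Value of covariates in total.** Model: logit P(event) = a(arm) + s·X, with X a standard normal baseline risk score. The intercepts are set so that the marginal rates stay at 27.5% and 22.5%. Power comes from the Fisher information at 1176 per arm. The values of s are assumptions.

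| s | c-statistic | conditional OR | SE of log OR | power | information relative to unadjusted |
|---|---|---|---|---|---|
| 0 | 0.50 | 0.765 | 0.0956 | 79.9% | 1.00 |
| 0.50 | 0.63 | 0.756 | 0.0978 | 81.6% | 1.045 |
| 0.75 | 0.69 | 0.745 | 0.1004 | 83.5% | 1.10 |
| 1.00 | 0.74 | 0.731 | 0.1036 | 85.7% | 1.17 |

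The first row is 79.9% rather than 80.0% because the two rates give an OR of 0.7654 before rounding. Check of the last row: |ln 0.731| / 0.1036 = 0.313 / 0.1036 = 3.02, against 0.267 / 0.0956 = 2.80 unadjusted. The squared ratio is about 1.17. The standard error rises, but the log odds ratio rises more.

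**3. Value of the extra covariates over the planned ones.** Simulation with 4000 trials per row and 1176 per arm. The planned covariates are one score with slope 0.4 (c about 0.60). The extra covariates are a second, independent score. Both strengths are assumed, and centre effects were not simulated.

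| slope of extra score | combined c | planned model | extended model | gain |
|---|---|---|---|---|
| 0 | 0.61 | 81.0% | 81.1% | 0.1 |
| 0.30 (weak) | 0.64 | 79.7% | 80.2% | about 0.5 |
| 0.50 (moderate) | 0.67 | 80.1% | 82.0% | about 2 |
| 0.75 (strong) | 0.71 | 80.4% | 84.0% | about 3.5 |
| 1.00 (very strong) | 0.76 | 81.3% | 86.8% | 5.5 |

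The Monte Carlo standard error of each power is about 0.6 points, so the weak case is within simulation error. The first row shows that a useless extra covariate costs nothing visible.

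**4. Room in the model.** Expected events: 0.25 × 2352 = 588. Intercept, treatment and the three planned covariates make 5 coefficients. ASA class as three indicators (an assumption), four comorbidities and Hb add 8. 588 / 13 is about 45 events per coefficient, so overfitting is no obstacle.

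**The case against.** The primary model is prespecified, short and legitimate. It delivers the promised power with no covariate credit, and the planned covariates can only add to that. Wanting a longer list is close to a preference. This stands to the extent that the point is a recommendation and not a correction.

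The article also gives no association between any of these variables and the composite. The subgroup section offers them as possible modifiers of benefit, which does not show that they predict outcome. This stands in full: the gain can only be given as a range, and its lower end is negligible.

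Three further inferences might tempt a reader, and the document does not support them:

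- **That the sentence on further variables leaves the primary result open to choice after the data are seen.** It governs secondary analyses only, and their covariates may be named in a statistical analysis plan that is not shown.
- **That chance imbalance in cardiac or renal disease would bias the estimate.** Randomisation protects against bias, and the confidence interval already allows for chance imbalance. The issue is precision.
- **That baseline creatinine is equally free to use.** The schedule of assessments describes creatinine as usual-care values obtained during or after randomisation. The definitions of milder kidney injury refer to a baseline without dating it. A pre-operative value for every patient is not shown.

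Adjustment also has some cost. Covariates may have missing values while the full analysis set includes everyone randomised, and the estimated odds ratio will not correspond directly to 0.765.

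**Conclusion.** The point holds as a missed efficiency gain. ASA class, four cardiovascular comorbidities and pre-operative Hb are recorded in any case, are plausibly prognostic on the protocol's own reasoning, and are left out of a primary model that has ample events to carry them.

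At 2352 evaluable patients, adding them raises power by about 0.5 to 5.5 points for a combined c-statistic of about 0.64 to 0.76, and by about 2 to 4 points for a moderate-to-strong score. These figures rest on three assumptions: planned covariates with a c-statistic near 0.60, an extra score independent of them, and no centre effects. The direction is secure; the size is not.

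It would be wrong to conclude that the trial is underpowered, that the primary analysis is invalid, or that strong predictors have been shown to be omitted. The 80% is met as stated, and no prognostic strength is documented.

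**What to change.** Before any unblinded analysis, including the interim, prespecify the primary mixed logistic model as treatment, age, cancer surgery, surgical risk class, ASA class, ischaemic heart disease, heart failure, peripheral vascular disease, previous stroke and pre-operative Hb, with random centre. Use the same model at the interim and at the final analysis. Keep the three-covariate model as a sensitivity analysis.

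Only pre-randomisation values should enter. Add creatinine only if a pre-operative value is recorded for essentially all patients. Keep delta Hb out: randomisation can occur at any time from surgery to day 3, so the day-3 value may already reflect the assigned strategy.

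Costs:

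- **Wording** in the protocol or analysis plan; no extra patients or visits.
- **A simple rule for missing covariates**, such as imputation from baseline data alone, so that all randomised patients stay in the analysis.
- **Interpretation.** The conditional odds ratio for the same 27.5% and 22.5% rates would be about 0.73 at a c-statistic of 0.74. The plan should say so and rely on the already planned rate difference and relative risk for the clinical reading.

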### Interim analyses

One formal unblinded interim analysis is scheduled after about 1450 patients with 90-day endpoint information in order to detect early superiority. This interim analysis will use a significance level of alpha = 0.001 such that the final analysis does not require adjusting for multiple testing. With this interim analysis, we will have 80% power to detect an odds ratio of 0.6, which corresponds to an OCCR difference in the order of 10%.

If the interim analysis turns out significant, the trial will be stopped, unless the Data Monitoring Safety Board (DMSB) recommends otherwise. The responsible study biometrician will perform the formal interim analysis, write a strictly confidential report and discuss the results exclusively with the Data Monitoring Safety Board. If the DSMC recommends continuing with the trial, the Sponsor, the steering committee, the investigators, and the study team will only receive the information that the interim analysis for early superiority was performed and discussed with the DSMC and that the trial continues. All respective documents and analysis scripts are kept on a dedicated file system to which only the biometrician and his assistant have access rights.

### Planned exploratory sub-group analyses

We hypothesise that the benefit from a liberal transfusion strategy increases with declining anaemia compensatory capacity.

We will therefore perform exploratory subgroup analyses byAge (< 80 versus ≥80 years),Gender (male/female),American Society of Anaesthesiology Physical Status classification [30],presence of cancer (y/n),ischaemic heart disease (y/n),heart failure (y/n),peripheral vascular disease (y/n),previous stroke (y/n),

Any resulting hypothesis requires confirmation in independent data.

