### Study population

A two-step approach will be used (Figs. 1 and 2): In step I, elderly patients (age ≥ 70 years) will be registered if scheduled for elective, non-cardiac surgery of intermediate or high risk. Written informed consent is obtained from the patients themselves or from their legally authorised representative/legal guardian.

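### The hypothesis on effect modification is graded, but age is examined only by a split at 80, which loses about 25-42% of the information on an age gradient that is roughly linear

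*Protocol article*

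**What the plan says.** Under Planned exploratory sub-group analyses the protocol article says: "We hypothesise that the benefit from a liberal transfusion strategy increases with declining anaemia compensatory capacity". The subgroup list follows as the consequence of that sentence. It has eight factors: age in two groups divided at 80, gender, "American Society of Anaesthesiology Physical Status classification", and presence or absence of cancer, ischaemic heart disease, heart failure, peripheral vascular disease and previous stroke. The section closes with the limit "Any resulting hypothesis requires confirmation in independent data".

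Two other places bear on the point. Study population sets the age range: "elderly patients (age ≥ 70 years) will be registered if scheduled for elective, non-cardiac surgery of intermediate or high risk". No upper limit is stated. Statistical analysis specifies "generalised linear mixed models adjusting for age, cancer surgery (y/n), type of surgery (intermediate- or high-risk), and incorporating centres as random effect". Age is therefore a covariate in the main model, with its functional form not stated. No treatment-by-age term, continuous or ordered, appears anywhere in the article.

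**The concern.** The hypothesis describes a gradient, and the analysis of age can show only a step. Under the split, patients aged 70 and 79 are treated as alike and patients aged 79 and 80 as different. The article gives no reason for expecting a change at 80.

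Age deserves more care than the other factors for two reasons. The Abstract and Background rest the case for the trial on the decline of functional reserve with age. Age is also plainly measured on a continuous scale in every patient, so grouping it throws away information already collected. At stake is how well the trial can describe whether and how the effect of liberal transfusion changes across the ages enrolled. Interaction analyses are weak in a trial sized for a main effect, so an avoidable loss is worth avoiding.

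**Working it through.** **1. The plan's own figure.** Sample size considerations gives 27.5% and 22.5%, OR 0.765, two-sided 5% and 80% power, on the normal approximation to log(OR).

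- Per-arm variance sum: 1/(0.275 × 0.725) + 1/(0.225 × 0.775) = 5.016 + 5.735 = 10.750.
- n per arm = (1.960 + 0.842)² × 10.750 / (ln 0.765)² = 7.849 × 10.750 / 0.0718 = 1175.9, so 1176 per arm and 2352 in total. This reproduces the plan.
- SE of the log OR = √(10.750/1176) = 0.0956.

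The plan states no figure for the subgroup analyses.

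**2. Information kept by the split.** Assume 1:1 allocation independent of age and an interaction linear in age on the log-odds scale. The share of information kept by the two-group variable is then approximately the squared correlation between age and the indicator of being 80 or over:

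r² = p(1 − p)(m₁ − m₀)² / SD²

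Here p is the share aged 80 or over, m₁ and m₀ are the mean ages above and below 80, and SD is the standard deviation of age. The loss is 1 − r².

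Two cases can be checked by hand:

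- Uniform from 70 to 95: p = 0.6, m₁ − m₀ = 87.5 − 75 = 12.5, SD² = 25²/12 = 52.08. So r² = 0.24 × 156.25 / 52.08 = 0.72.
- 70 plus an exponential with mean 10: the formula reduces to r² = [p/(1 − p)] × (10/10)² with p = e⁻¹ = 0.368. So r² = 0.368/0.632 = 0.58.

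**3. Power with the split.** For an interaction with 80% power as a linear term, power with the split = Φ(2.802 × √r² − 1.960).

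**4. Results.** The article gives no age distribution, so every row is an assumption. The truncated-normal rows are simulated, cut off at 70 and 100.

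| Assumed ages | Share aged ≥80 | r² | Loss | Power with split |
|---|---|---|---|---|
| Uniform 70-90 | 50% | 0.75 | 25% | 68% |
| Uniform 70-95 | 60% | 0.72 | 28% | 66% |
| Truncated normal, 20% or more aged ≥80 | 21-58% | 0.60-0.69 | 31-40% | 58-64% |
| 70 + exponential, mean excess 6-10 years | 19-37% | 0.58-0.65 | 35-42% | 57-61% |
| Truncated normal, few aged ≥80 | 4-15% | 0.32-0.52 | 48-68% | 36-52% |

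The first four rows give the range of 25-42% lost and 57-68% power. The last row shows that the loss can pass one half when few patients are 80 or over. Shape matters there too: 70 plus an exponential with mean 5 has 13% aged 80 or over and loses 37%.

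**5. How large an interaction has 80% power?** With age in SD units, the interaction coefficient has about the same SE as the main effect, 0.0956. Power of 80% then needs a shift of 2.802 × 0.0956 = 0.268 in the log OR per SD of age. That equals the whole planned effect, |ln 0.765| = 0.268. For an interaction half that size, the linear term has Φ(1.401 − 1.960) = 29% power. The split has Φ(1.401 × √r² − 1.960), which is 19% at r² = 0.58 and 23% at r² = 0.75.

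**The case against.** The strongest case against the point has four parts.

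- **The hypothesis is about compensatory capacity, not age.** Age is one of eight factors. Gender and the five yes/no conditions lose nothing through a cut. A reader might infer that a quarter or more of the information on the whole capacity hypothesis is lost. The article does not support that, and the loss is confined to age.
- **Monotone is not linear.** If benefit stepped up at 80, the same r² would work in reverse: the split would be the efficient analysis and the linear term would lose. This stands, and it is why the continuous term should be added beside the split with a check on shape. The article offers no reason to expect a step at 80.
- **The trial is too small for interactions anyway.** Step 5 bears this out: 80% power needs an interaction as large per SD of age as the planned main effect, and for half of that both analyses are weak. So it would be too strong to say that the split is what would make the trial miss effect modification. Sample size is the larger limit, and the split adds to it.
- **The analyses are exploratory.** The section requires independent confirmation, and a prespecified cut guards against a threshold chosen from the data. Both are true. They limit what may be claimed afterwards, but they give no reason to use only the less efficient analysis of data already held. A prespecified continuous term guards against a chosen threshold equally well.

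A reader might also infer that ASA class will be analysed without regard to its order. The article lists ASA class with no coding or grouping, so no criticism of it can be drawn. The analysis plan, not shown, may add a continuous age term. The two-group comparison is nevertheless what the protocol article itself fixes for age.

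**Conclusion.** The point holds as a minor one. The article states a gradient and fixes a two-group comparison as its only analysis of age. The size given rests on two assumptions that the documents do not supply: an interaction roughly linear in age, and an age distribution with about 20% or more of patients aged 80 or over.

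Nothing in the primary analysis, its significance level, the sample size or the interim analysis depends on this choice. Nor is the article in error or in contradiction with itself here. It names a less efficient method than its own hypothesis and data allow.

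**What to change.** In Planned exploratory sub-group analyses, add a treatment-by-continuous-age interaction to the logistic mixed model described under Statistical analysis, as the analysis of the age gradient. Use a linear term, with a spline as a check for non-linearity. Report the treatment odds ratio with its 95% interval at ages such as 70, 75, 80 and 85. Keep the comparison of under 80 with 80 or over for display. Keep the exploratory label and the sentence on independent confirmation.

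The cost is a sentence or two of wording and slightly more analysis work. No new data are needed and the primary analysis is unchanged.
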